#### Mechanistic analysis sample size

Estimates of the mediation parameters from Hirsch, Krahe et al. [27] as follows: standardised estimate of the a path (effect of intervention on mediator) = 0.5, b path (effect of mediator on outcome) = 0.2, and c’ path (direct effect of intervention on outcome) = 0.15, providing parameters for Monte Carlo simulations with 10 K repetitions to calculate power in Mplus [47], a sample size of 268 would give > 99% power to detect the mechanistic action of the intervention on interpretation bias (a path), and 83% power to detect the indirect or mediated (a x b) effect of the intervention on GAD-7 via interpretation bias.

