### Sample size {14}

#### Clinical efficacy sample size

For a two-sided independent samples *t*-test, alpha = 0.05, assuming one baseline and three post-randomisation measures with correlation rho = 0.5 (conservative based on baseline − T2 estimate from Hirsch, Krahe et al., 2021 [27] of rho = 0.42), deflation factor of 0.5 [45], and accounting for 35% attrition (based on online CBT: [46]), we will need 268 participants in total (134 per arm) to have 90% power to detect a GAD-7 effect size of 0.35 (powered slightly conservatively compared to T2 GAD-7 effect size of 0.40 from Hirsch, Krahe et al., 2021 [27]).

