### Methods for additional analyses (e.G. Subgroup analyses) {20b}

#### Analysis of the mechanistic outcome/mediation analysis

To estimate the extent to which the intention to treat RELAX vs UC intervention effect on anxiety (GAD-7) at 8 weeks (primary) or 36 weeks (secondary) is mediated by interpretation bias (measured using the Recognition Test) at 4 weeks, we will use linear structural equation models estimated using full information maximum likelihood estimation to fit mediation models. We will fit two separate structural equation models for the 8-week and 36-week GAD-7 outcome measures, each fitting two equations: one with the 4-week interpretation bias (RT) mediator as the dependent variable and the other with the GAD-7 outcome as the dependent variable with the RT mediator as an independent variable. Both mediator and outcome models will have arm as a binary independent variable, include the three randomisation stratification factors and the weeks of gestation at baseline variable as independent variables, and will include baseline GAD-7 and interpretation bias (RT) measures as independent variables.

The indirect (or mediated) effect will be calculated in each case by multiplying the estimate of the effect of the intervention on the interpretation bias mediator by the estimate of the effect of interpretation bias on the GAD-7 outcome. For this indirect effect, we will present the percentile bootstrap confidence interval from bootstrapping with 1000 repetitions [51]. We will also present this proportion of the total effect that mediated for each model, calculated as the indirect effect estimate divided by the total effect estimate, multiplied by 100.

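### The 83% power for the mediated effect assumes all 268 participants are analysed; at the plan's own 35% attrition it is about 64%

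*Protocol article*

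**What the plan says.** Two adjacent paragraphs under Sample size {14} use the same total.

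- *Clinical efficacy sample size*: 268 (134 per arm) is the number to randomise, after "accounting for 35% attrition", for 90% power on the GAD-7.
- *Mechanistic analysis sample size*: path values come from an earlier online trial. The first is given as "standardised estimate of the a path (effect of intervention on mediator) = 0.5"; the path from mediator to outcome is set at 0.2 and the direct effect at 0.15. Power comes from "Monte Carlo simulations with 10 K repetitions to calculate power in Mplus". With all 268 counted, the paragraph puts the a path above 99% and, for the indirect effect, claims "83% power to detect the indirect or mediated (a x b) effect of the intervention on GAD-7 via interpretation bias". It does not mention attrition.

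For the analysis itself, the mediation section under {20b} says "we will use linear structural equation models estimated using full information maximum likelihood estimation to fit mediation models". The 4-week Recognition Test is the mediator and the 8-week GAD-7 the outcome. Both equations are adjusted for baseline GAD-7 and baseline interpretation bias, and the indirect effect gets a percentile bootstrap interval.

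**The concern.** The same 268 is gross of loss in the first paragraph and treated as fully analysed in the second. If 35% are lost, the mediation model has about 174 people with an outcome, and a power figure for 268 overstates what the trial can show.

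This matters because Objectives {7} makes mediation by interpretation bias the mechanistic focus, and the Mechanistic outcome section lists the mediated effect on 8-week GAD-7. Someone who trusts 83% will give a null indirect effect more weight than the data can bear. That last point is an inference about how the result may be read. The article does not say that a null will be taken as evidence against the mechanism.

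**Working it through.** **Inputs.** Paths a = 0.5, b = 0.2, c′ = 0.15; N = 268; attrition 35%; 1:1 allocation (all from the article). Two-sided alpha of 0.05 is stated for the clinical calculation and assumed here for mediation. Loss is taken as completely at random.

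**Step 1: is attrition already in the 268?** A two-sample t-test for d = 0.35 at 90% power needs about 172 per arm. The deflation factor gives 172 × 0.5 = 86, and 86/0.65 ≈ 133 (87/0.65 ≈ 134). So 268 already contains the loss, and the expected analysed number is 268 × 0.65 ≈ 174.

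**Step 2: closed form with fully standardised paths.**

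- Mediator residual variance: 1 − a² = 0.75.
- Outcome residual variance: 1 − (b² + c′² + 2ab c′) = 1 − (0.04 + 0.0225 + 0.03) = 0.9075.
- SE(a) = √(0.75/N); SE(b) = √(0.9075/(0.75 N)) = 1.1/√N.
- SE(ab) = √(a² SE(b)² + b² SE(a)²); approximate power = Φ(z − 1.96).

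| | N = 268 | N = 174 |
|---|---|---|
| z for a | 0.5/0.0529 = 9.45 | 0.5/0.0657 = 7.62 |
| z for b | 0.2/0.0672 = 2.98 | 0.2/0.0834 = 2.40 |
| power for b (close to the joint test, as a is near certain) | Φ(1.02) = 85% | Φ(0.44) = 67% |
| z for ab (Wald) | 0.1/0.0352 = 2.84 | 0.1/0.0437 = 2.29 |
| power for ab (Wald, approximate) | Φ(0.88) = 81% | Φ(0.33) = 63% |

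The b path is the bottleneck; the a path is never in doubt.

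**Step 3: Monte Carlo, 10,000 replicates, the method the article names.**

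| Analysed N | Loss | Wald test of ab | Joint test of a and b |
|---|---|---|---|
| 268 | none | 83% | 83–84% |
| 241 | 10% | 79% | 80% |
| 228 | 15% | 76% | 78% |
| 201 | 25% | 71% | 74% |
| 174 | 35% | 64–65% | 66–67% |

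The first row reproduces the printed figures (83%, with the a path at 100%). A percentile bootstrap gives about 84–85% at 268 and 66–69% at 174.

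**Step 4: does full information maximum likelihood rescue it?** Take the most favourable pattern: arm and mediator observed in all 268, with only the outcome missing in 35%. Power is 64% (Wald) or 66% (joint). People without an 8-week GAD-7 contribute to the a path, which has power to spare, and nothing to the b path.

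**Step 5: other readings of the paths.** With a as a 0/1-arm mean difference of 0.5 SD, a-path power at 268 is 98–99%, short of the stated figure, and indirect power at 174 is 48–69% depending on the test. With residual variances set to 1, indirect power at 268 is 89–90%, which does not match 83%, and it is 71–75% at 174. No reading tried gives 83% at 174.

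**The case against.** The strongest reply is that 64% does not describe the planned analysis.

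- **Test.** The plan uses a percentile bootstrap, which gives 66–69% at 174. This stands, and it is why a range should be quoted.
- **Covariates.** The model adjusts for baseline GAD-7 and baseline Recognition Test; the simulation does not. The clinical paragraph gives 0.42 (observed) and 0.5 (assumed) for the GAD-7 correlation. The article gives no correlation for the Recognition Test, so I varied it from 0 to 0.5 as an assumption, with independent baseline covariates and 4,000 replicates. Wald power at 174 then runs from 57% to 78% (joint up to 80%). Adjustment may help or hurt, because a baseline that explains the mediator leaves less of it to estimate b. The same settings at 268 give 76% to 92% by Wald, so attrition costs 14 to 19 points in each. The printed 83% is reproduced without covariates, and 64% is its direct counterpart.
- **Attrition.** The 35% is one allowance borrowed from online CBT, not a forecast for weeks 4 and 8. The Introduction reports excellent retention in the closest earlier online trial, and vouchers and prompts are planned. Loss may well be smaller, but even 15% leaves about 76%.
- **Importance.** The primary mechanistic outcome is the 4-week between-arm difference in interpretation bias, which is the a path. Its power stays above 99% on the reading that reproduces the article. This limits the seriousness of the error without making the 83% right.

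**Conclusion.** The point holds. The printed 83% is the power with no loss to follow-up, and it sits directly below a calculation that plans for 35% loss. Like for like, the power at the plan's own analysed number is about 64% (66–69% with a joint or bootstrap test). The chance of missing a true mediated effect of the assumed size rises from 17% to about 36%.

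This rests on fully standardised paths (the reading that returns both printed figures), two-sided 0.05, data missing completely at random, and 35% loss applying at 8 weeks. The simulation at 268 is itself correct; the error is that the attrition allowance was not carried into it. The consequence is confined to the mediated effect. The efficacy sample size, the primary outcome and the a-path power are not affected.

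**What to change.** Re-run the existing Mplus simulation at the expected number with both the 4-week mediator and the 8-week outcome (174), and replace the 83% with the result: about 64–66% for the indirect effect at the stated paths by the Wald or joint test. Name the test used. If 4- and 8-week retention is better than 65%, quote the power at that retention and say so. If the authors want credit for baseline adjustment, they should put the covariates and their assumed correlations into the simulation and state them. Add one sentence that a non-significant indirect effect will not be interpreted as absence of mediation, and that the estimate will be read with its bootstrap interval.

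The cost is one re-run and a text correction, with a less favourable figure in print. Trial conduct does not change. Holding 83% under 35% loss would take about 268/0.65 ≈ 413 randomised, which shows the size of the gap and is not a request to enlarge the trial.

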### Recruitment {15}

We expect that a higher proportion of participants will be recruited from the combined NHS sites. Particular site targets will be determined according to the timing of site opening. A minimum of one quarter of participants are expected to be recruited from the KCL route.

#### NHS sites

The study aims to recruit 268 participants. We will recruit participants through one of the four participating NHS hospital sites (Guy’s and St Thomas’ NHS Foundation Trust (GSTT), King’s College Hospital NHS Foundation Trust (KCH), Epsom and St Helier University Hospitals NHS Trust (ESTH) and Mid Cheshire Hospitals NHS Foundation Trust (MCHT)). Staff who are part of the potential participants’ direct care team will screen the medical records of women booked to receive antenatal care at each participating site to identify potentially eligible participants and notify them about the study. In addition, pregnant women will be approached in antenatal clinic waiting areas and during routine antenatal appointments and informed about the study, or given study details, such as the Participant Information Sheet or study flyers.

Posters advertising the study will be displayed in and around antenatal waiting areas and clinic rooms, utilising a QR code for ease of signposting to the RELAX platform. Flyers and business cards will also be utilised, dependent on local permission, for potential participants to take study details with them or leave their details so that they can be contacted by the RELAX research team.

At some of the NHS sites, research midwives (including “flexible” clinical research midwives) will also provide information on the study to potentially eligible women via email and phone, following screening of clinical records, and signpost them to the platform (website).

Other NHS recruitment initiatives will include providing details about the study during antenatal ward rounds and meetings, patient classes, and via research circulars and events. In addition, RELAX will be listed on NHS site-specific maternity apps seen by pregnant women, so that all pregnant women registered at the participating site will receive push notifications about the RELAX study.

#### Other recruitment routes

The research team at King’s College London (KCL), supported by PPIE advisers, partner organisations, charities, third sector organisations and affiliated communications teams will share information about the study via social media and community organisations. This will include advertising on channels such as Instagram [48], Facebook [49], and X [50], and approaching pregnancy support groups community organisations and charities and requesting that they promote the study in their venues, through events and on their social media platforms. This community and social media recruitment approach has been adopted using testimonies and community endorsement with the aim of recruiting a diverse range of participants, including those often disproportionately excluded from research, such as Black and Asian women. Participants recruited via these recruitment routes will be allocated to the “KCL” recruitment site strata. In addition, posters will also be displayed in antenatal waiting areas at non-participating NHS sites and health care facilities across the UK where permission has been given. A small number of GP practices in South London have also been invited to identify pregnant women who may be eligible for the trial and recruit participants as Participant Identification Centres (PIC) sites for the study. Participants recruited via these methods will also be allocated to the “KCL” recruitment site strata.

## Assignment of interventions: allocation

### Sequence generation {16a}

Stratified randomisation will be carried out via the RELAX platform by an embedded computer-generated algorithm developed by Avegen and embedded in the platform. Randomisation will be at the individual level, in a 1:1 ratio using randomly permuted blocks with varying block sizes. The algorithm selects the next appropriate allocation for an individual based on their stratification variable values.

Stratification is by.recruitment site (either one of the four participating NHS Trusts: GSTT v KCH v ESTH v MCHT) or KCL (pathway covering all other social media and community recruitment routes, including non-participating NHS sites recruitment, e.g. via posters or GP practices)parity (previous livebirths vs no previous livebirths)previous pregnancy complications (no pregnancy complications vs some pregnancy complications (past or current)).

### Concealment mechanism {16b}

Participants are randomised after eligibility criteria are confirmed.Participants will be randomised to either the RELAX intervention alongside UC or receive UC alone. The complete randomisation list sequence will be concealed from the investigators including the Chief Investigator (CI) and statisticians. The research team become aware of a single individual arm allocation at the point of randomisation by viewing the participant’s record on the password protected researcher’s interface platform. The researcher’s interface is built and hosted by Avegen and is used by the researchers to enrol and monitor participant progress. It is also where participant entered assessments and session data can be viewed and edited if verified to be missing or incorrect by the participant. Any edits of this sort are time stamped with the researchers’ initials for transparency. The researcher’s interface also holds researcher data, e.g. participant contact and payment logs.

Participants will be made aware of their randomisation arm via a message on the platform after submitting their baseline assessment. When viewing the Dashboard, it will either present the RELAX sessions and assessments (RELAX + usual care arm) or just the assessments (Usual care arm). Each session or assessment is available and unlocked once a participant has reached the applicable session or assessment timepoint.

### Implementation {16c}

The bespoke RELAX randomisation algorithm has been built into the platform by Avegen’s data team and programmers. Stratified randomisation will be carried out via the RELAX platform by Avegen in a 1:1 ratio using randomly permuted blocks with varying block sizes. Stratification is by recruitment site (GSTT vs KCH vs ESTH vs MCHT vs KCL), parity (0 vs not 0), and pregnancy complications (no pregnancy complications vs pregnancy complications). The information needed to classify participants based on the stratification variables will be gathered via the screening questionnaire (and verified on the study outline call). This information will be entered by the researchers into the researcher’s interface, providing the information required for randomisation.

## Assignment of interventions: blinding

### Who will be blinded {17a}

The CI, Co-Investigators and Principal Investigators at each study site will be unblinded at the individual level but will remain fully blinded at the group level (will not see data summarised by arm) until they review the statistical report, at which point they will become fully unblinded. The senior statistician will not have access to the randomisation list or the database platform at any point in the trial and will remain fully blinded until review of the first draft of the statistical reports for checking, when they will become fully unblinded. The trial statistician will be fully blinded until approval of the statistical analysis plan, after which they will be fully unblinded so they can inspect and utilise platform usage/intervention-related data. The Trial Coordinator, Research Assistant(s), Research Midwife, and any other members of the study team (e.g. students/volunteers working on the study) will be unblinded at the individual level only. The only individuals that will be able to summarise/see data by arm prior to the review of the statistical report are the trial statistician and the members of the Data Monitoring and Ethics Committee (DMEC), with the latter remaining partially blinded (i.e. arms shown as A/B) at the group level. The Trial Steering Committee (TSC) will remain blinded at both group and individual levels throughout the trial. As clinical staff in each investigation site are unblinded at the individual level, they will be able to reveal an individual’s allocation if needed.

### Procedure for unblinding if needed {17b}

If study team members are unintentionally unblinded, this will be recorded as a protocol deviation. Implications for analysis will be discussed with the DMEC. Any deviations will be documented and reported to the relevant authorities (e.g. Medicines and Healthcare products Regulatory Agency (MHRA)) as soon as possible.

As participants are not blinded, there is no need to have a process for unblinding participants.

## Data collection and management

### Plans for assessment and collection of outcomes {18a}

Participant sessions and assessments will be completed online, with data inputted by the participant into the RELAX platform built and hosted by Avegen. Each participant will have their own unique ID and enter the platform using their email address and their own set password. The platform therefore delivers the intervention and collects the data, which is saved into the database hosted by Amazon Web Services (AWS).

Participants self-complete all questionnaires for the assessments online. There is, however, the option for participants’ data to be collected from the participant in a telephone call with the researcher. In such instances, the researcher will input the participant’s responses via the researcher’s interface. This can be done with approval of the CI and in cases where a participant is unable to complete the assessments online themselves and require this additional support.

### Plans to promote participant retention and complete follow-up {18b}

Participants will receive £25 in online vouchers for each of the four assessments they complete (which is routine practice in mental health trials) to compensate for their time and to maximise data collection rate. Furthermore, there will be a prize draw for anyone who completes the screening questionnaire with the chance to win a £50 voucher. Members of our PPIE advisory group have favoured the idea of running a prize draw, which will occur every 3 months throughout the recruitment period.

Participants will receive email notifications to complete their assessments 1 week prior to their assessment opening, and on the day of assessment opening through the online RELAX platform. Automatic reminders will be sent a week after an assessment has been opened if it has not been completed. Researchers will also prompt participants at least three times after an assessment is opened if it remains incomplete. Prompts may be via telephone, text message or email. T1 and T2 assessments remain open for 3 weeks, and T3 assessments for 8 weeks following the assessment’s due date. Participants who withdraw or are lost to follow-up will not be replaced.

### Data management {19}

Online responses will be collected using the RELAX platform. All data collected will be stored using Amazon Web Services (AWS). Any other screening data will be collected by the study team and uploaded to the researcher interface, feeding into the database on AWS.

To ensure data quality, data checking will be carried out throughout the trial. Data anomalies will be queried by the trial statistician and corrected by the team where possible (as much of the source data will be entered directly into the Avegen platform by the participants) prior to statistical analysis.

### Confidentiality {27}

All personal data collected during screening and recruitment will be stored as password-protected files on KCL secure servers (or physical paper copy documents or items such as audio recorders in locked storage on KCL property). NHS secure servers will store information held by the Research Midwife, such as recruitment logs and if a person has consented to be contacted about the project by the research team. Personal data of participants and potential participants will also be stored on the RELAX platform and researcher interface on Avegen’s secure database. Only researchers directly involved in the study will have access to the data. Participants’ personal data will be retained for up to a year following the end of the clinical trial. Personal data of potential participants will be retained until the end of the recruitment period. During the trial, all data will be pseudonymised using unique identification numbers and stored without identifying information (names, email addresses, phone numbers). Once the trial is completed, data will be stored anonymously and securely for 12 years.

### Plans for collection, laboratory evaluation and storage of biological specimens for genetic or molecular analysis in this trial/future use {33}

Not applicable as no biological samples are to be collected.

## Statistical methods

### Statistical methods for primary and secondary outcomes {20a}

A statistical analysis plan (SAP) has been drafted by the senior statistician and approved by the DMEC and TSC. The SAP is available on request from the corresponding author and trial statisticians.

The primary population for analysis will be the intention to treat (ITT), defined as all randomised participants, analysed in the arms they were randomised to, regardless of which intervention they received.

